### Intervention

4.5

Informed consent shall be diligently obtained from all participants, elucidating the potential advantages associated with embracing a health-conscious lifestyle, encompassing regular exercise and a nutritionally balanced diet. The study's intervention will be bifurcated into distinct groups: the study group, exclusively undergoing acupuncture treatment, and the control group, solely subjected to Fenmutong administration. The intervention duration for both groups is stipulated at three menstrual cycles. The administration of acupuncture treatments for the study group will be executed by adept professional acupuncturists possessing a minimum of 2 years of practical experience in acupuncture techniques.

### Acupuncture treatment

4.6

This study is conducted in accordance with the Standards for Reporting Interventions in Clinical Trials of Acupuncture (STRICTA) guidelines [21], thereby ensuring a comprehensive and transparent approach to acupuncture treatment for POI. The selection of acupoints is based on the Zang-fu organ system, the Yin-Yang theory, and clinical guidelines, with two sets of acupoints alternately applied. Sterilised, single-use needles from the Huatuo Suzhou Medical Appliance Factory are employed following the disinfection of the skin. The methods of needle manipulation for each acupoint featured in this study are presented in Table 2 in meticulous detail. The STRICTA checklist, which details the study's compliance with these standards, is included as supplementary material. Each acupuncture session, with a standard duration of 30 min and conducted three times a week, is designed to achieve de qi, a sensation integral to acupuncture efficacy. The treatment regimen is meticulously documented in accordance with the STRICTA guidelines, from the anatomical specifics and needle manipulation techniques to the consistency across all sessions, spanning up to three menstrual cycles.

**Table 2 tbl2:** Acupuncture protocol.

Acupoints	Location	Method
Set 1		
CV-4 (Guanyuan)	On the anterior median line of the lower abdomen,3cun below the navel	1.0–1.5cun perpendicularly insertion
EX-CA1 (Zigong)	On the lower abdomen, 4cun below the navel, 3cun lateral to Zhongji (RN-3)	1.0–1.5cun perpendicularly insertion
ST-29 (GuiLai)	On the lower abdomen,4 cun below the umbilicus,and 2 cun lateral to the anterior midline.	1.0–1.5cun perpendicularly insertion
CV-3 (Zhongji)	On the anterior median line of the lower abdomen,4cun below the navel	1.0–1.5cun perpendicularly insertion
RN-12 (Zhongwan)	On the anterior median line of the upper abdomen, 4cun below the navel	1.0–1.5cun perpendicularly insertion
ST-36 (Zusanli)	3 cun directly below Dubi,and one finger-breadth lateral to the anterior border of the tibia.	1.0–1.5cun perpendicularly insertion
SP-10 (Xuehai)	2 cun above the upper border of the medial patella	1.0–1.5cun perpendicularly insertion
LR-3 (Taichong)	On the dorsum of the foot, in the depression proximal to the first metatarsal space	1.0–1.5cun perpendicularly insertion
Set2		
BL-18 (Ganshu)	On the back, under the spinous process of the 9th thoracic vertebra, 1.5 cun laterally	0.5–0.8cun diagonally insertion
BL-20 (Pishu)	On the back, under the spinous process of the 11th thoracic vertebra,1.5 cun laterally	0.5–0.8cun diagonally insertion
BL-23 (Shenshu)	On the back, under the spinous process of the 2nd lumbar spine,1.5 cun laterally	0.5–0.8cun diagonally insertion
BI-26 (Guanyuanshu)	On the back, under the spinous process of the 5th lumbar spine,1.5 cun laterally	0.5–1.0cun diagonally insertion
BL-32 (Ciliao)	In the region of the sacrum, between the posterior superior iliac spine and the posterior median line, in the 2nd posterior sacral foramen	2.5–3.0cun oblique insertion to the 2nd posterior sacral foramen
SP-6 (Sanyinjiao)	On the medial side of the shank, 3cun above the medial malleolus, by the posterior of the tibia	1.0–1.5cun perpendicularly insertion
KI-3 (Taixi)	On the medial side of the foot, posterior to the medial malleolus, in the depression between the tip of the medial malleolus and the tendon calcaneus	0.5–1.0cun perpendicularly insertion

Note: Two sets of acupoints will be used; each set will be used on alternate treatments.

### Fenmutong administration

4.7

The administration of Fenmutong treatment commences on the fifth day of menstruation specifically for participants diagnosed with POI assigned to the control groups. Initially, participants undertake oral administration of 2 mg estradiol tablets (brick-red tablets) daily for a consecutive period of 14 days. Subsequently, they transition to the oral intake of estradiol 2 mg + dydrogesterone 10 mg (yellow tablets) for another 14 consecutive days. A single course of this treatment spans 28 days. In the event of menstruation occurring during the medication period, the medication is recommenced from the 5th day of the subsequent menstrual cycle. If menstruation does not transpire, the subsequent course is initiated on the 7th day after the cessation of medication. The entirety of the treatment protocol extends across three menstrual cycles.

For participants experiencing amenorrhea at the time of consultation, immediate initiation of medication on the same day is permissible. Conversely, participants with infrequent menstruation should commence medication on the 5th day of the menstrual cycle, following the previously outlined methodology.

## Outcome measures

5

### Primary outcome: change in FSH levels

5.1

The principal outcome measure in this study revolves around the alteration observed in FSH levels. This metric serves as a pivotal gauge to evaluate the effectiveness of acupuncture treatment when employed as an adjunctive therapy for POI. The data collection process is bifurcated into two distinct time points: the baseline assessment conducted prior to the study's initiation and a subsequent assessment following the culmination of three menstrual cycles of acupuncture treatments. This meticulous approach aims to provide comprehensive insights into the impact of acupuncture on FSH levels over the specified duration, thereby contributing to the overall assessment of its therapeutic efficacy for POI.

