## Abstract

**Background:**

Premature ovarian insufficiency (POI), a modifiable cause of infertility with substantial implications for women's well-being, prompts the exploration of efficacious adjunctive treatments. Acupuncture emerges as a promising therapeutic avenue; however, the nuanced effects of acupuncture in POI warrant more comprehensive investigation. The intricate mechanisms dictating individualized responses remain elusive. This trial seeks to assess the effectiveness of acupuncture as an adjunctive treatment for POI, concurrently delving into the impact of transcriptome analysis on peripheral blood to unravel the underpinnings of these individual variations. The overarching objective is to enrich our comprehension of acupuncture's therapeutic potential in the context of POI, with a view to advancing holistic patient care.

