**Methods/design:**

Constituting an open-label, nested case-control study, this research endeavors to enroll 108 women diagnosed with POI. Participants will be randomly assigned in a 1:1 ratio to either the study group or the control group, each comprising 54 subjects. Ten patients from each group meeting specific criteria will partake in transcriptome analysis. An additional 10 subjects meeting the study criteria will form a healthy control group. The study group will exclusively undergo acupuncture treatment, while the control group will solely receive Fenmutong. Acupuncture sessions, administered thrice weekly across three menstrual cycles from the fifth day of menstruation, constitute the intervention. Primary outcome measurement rests on Follicle-Stimulating Hormone (FSH) levels, supplemented by secondary assessments encompassing biometric features, hormone biomarkers, anxiety and depression scores, and transcriptome analysis. Baseline measurements precede intervention, with post-intervention evaluations following. The study endeavors to discern specific genes linked to individualized responses to acupuncture. Data analysis, employing SPSS 25.0 software, incorporates a meticulous examination of peripheral blood samples for transcriptome analysis. The investigation aspires to shed light on genetic determinants influencing the effects of acupuncture on women with POI, thereby fostering elevated standards in patient care and management.

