**Discussion:**

This study pivots on the principal objective of scrutinizing the efficacy of acupuncture as an adjunctive treatment for POI. Beyond effectiveness, it undertakes an exploration of the intricate mechanisms underlying the diverse responses exhibited by individuals in the context of acupuncture, augmenting the depth of understanding in this therapeutic domain.

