Recent years have witnessed a rise in POI incidence, necessitating an in-depth investigation into its pathogenesis and treatment mechanisms. The advent of transcriptome sequencing technology in 1997 has revolutionized the study of POI's underlying mechanisms. Transcriptome sequencing not only serves as the foundation for identifying new POI-related genes but also facilitates the analysis of immune-related gene regulation, establishing correlations between different genes involved in POI pathogenesis. With approximately 90 genes currently linked to POI, its genetic heterogeneity becomes evident. For instance, studies exposing rats to environmental toxicants and utilizing transcriptome sequencing technology have identified DNA damage repair defects as pivotal in the pathogenesis of POI [[16], [17], [18]].

In this study, our primary objective is to gain a comprehensive understanding of the physiological significance of ovarian dysfunction in POI patients through peripheral blood transcriptome sequencing technology. The interactions between genes and ovarian function play a crucial role in elucidating the association between acupuncture action genes and individual differences observed in ovarian function recovery. To achieve these goals, we have designed a nested case-control study to evaluate the additional benefits of acupuncture treatment for women with POI. Additionally, we aim to investigate the mechanism underlying individual variations in response to acupuncture treatment, utilizing transcriptome gene sequencing analysis on peripheral blood samples. By employing this approach, we aim to systematically explore the potential mechanisms behind the observed individual curative effect differences with acupuncture in women with POI.

Through this research endeavor, we aspire to contribute valuable insights into the therapeutic effects of acupuncture for POI and shed light on the intricate interactions between genes and ovarian function. By understanding the underlying mechanisms, we hope to identify factors influencing the efficacy of acupuncture treatment in women with POI, paving the way for more personalized and effective treatment strategies for this condition. Ultimately, our study aims to contribute to the advancement of knowledge in the field of POI research, potentially improving the quality of life and outcomes for affected individuals.

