### Study design

4.1

The proposed investigation adopts an open-label, nested case-control study design to be conducted at Shenzhen Maternity and Child Healthcare Hospital. A total of 108 participants diagnosed with POI will be recruited for the study, and subsequent random assignment will be executed to allocate these patients into either the study group or the control group. The allocation ratio is set at 1:1, ensuring an equal distribution of 54 subjects in each group. Prior to the commencement of any intervention, explicit informed consent will be procured from all participating patients through the endorsement of a consent form administered by the researchers.

Patients comprising the study group will exclusively undergo acupuncture treatment, while those in the control group will exclusively receive Fenmutong. To gain deeper insights into the mechanisms contributing to individual variations in the therapeutic outcomes of acupuncture, a subset of 10 patients from each group will undergo transcriptome analysis. This subset will encompass patients experiencing a serum FSH level decrease of ≥30 % post-acupuncture intervention, alongside those displaying a decrease of <30 % in serum FSH levels following the intervention. The trial's procedural flow is visually represented in Fig. 1, offering a comprehensive overview of the various stages and interventions integral to the study. Additionally, Table 1 provides meticulous details on the data collection process, delineating specific data points and measurements crucial for the comprehensive execution of the research.

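### The stated question is acupuncture as an adjunct, but the arms compare acupuncture alone with Fenmutong alone, so no add-on effect can be estimated

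*Protocol article*

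**What the plan says.** **The question.** The protocol article describes its aim as an adjunctive or additional effect in several places:

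- Abstract, Background: "This trial seeks to assess the effectiveness of acupuncture as an adjunctive treatment for POI".
- Abstract, Discussion, where it is called the principal objective: "scrutinizing the efficacy of acupuncture as an adjunctive treatment for POI".
- Section 3 (Background), as the purpose for which the study was designed: "to evaluate the additional benefits of acupuncture treatment for women with POI".
- Section 5.1 (Primary outcome), on what the change in FSH is for: "to evaluate the effectiveness of acupuncture treatment when employed as an adjunctive therapy for POI". Section 5.2 repeats this text.

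**The arms.** The treatment groups are defined three times, always in the same way:

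- Abstract, Methods/design: "The study group will exclusively undergo acupuncture treatment, while the control group will solely receive Fenmutong".
- Section 4.1 (Study design): "Patients comprising the study group will exclusively undergo acupuncture treatment, while those in the control group will exclusively receive Fenmutong".
- Section 4.5 (Intervention): "the study group, exclusively undergoing acupuncture treatment, and the control group, solely subjected to Fenmutong administration".

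Section 4.7 confirms who takes Fenmutong: it is started "specifically for participants diagnosed with POI assigned to the control groups". No section describes acupuncture given together with Fenmutong, hormone replacement or any other treatment.

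**The concern.** An adjunctive effect is the gain from adding a treatment to one that the patient already receives. Estimating it requires the same background treatment in both arms, with the new treatment added in one. Here each arm receives a single, different treatment, so the randomised comparison answers another question: whether acupuncture does better than Fenmutong when used in its place.

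The mismatch affects the interpretation of the primary outcome whichever way the result falls. A favourable result read against the stated objective would appear to support adding acupuncture to existing treatment, which no participant receives. A null or unfavourable result would appear to show no add-on benefit, when it would show only that acupuncture alone did not beat an active drug that the acupuncture arm did not take. No analysis of these arms can supply the missing contrast.

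**Working it through.** **Step 1. Define the two effects.** Let m(·) be the mean fall in FSH under a treatment, A acupuncture and F Fenmutong. Fenmutong is taken as the background because it is the only other treatment in the trial.

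- Effect named in the objective (add-on): m(A+F) − m(F).
- Effect the arms deliver (substitution): m(A) − m(F).

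**Step 2. Relate them.** By subtraction:

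add-on = [m(A) − m(F)] + [m(A+F) − m(A)].

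The first bracket is the trial's contrast. The second is the effect of adding Fenmutong to acupuncture. Nobody is assigned A+F, so the trial holds no data on the second bracket: 54 women receive A, 54 receive F, and 0 of 108 receive both.

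**Step 3. Use the plan's own figures.** Section 6.4 assumes m(A) = 20 and m(F) = 14.5 IU/L. The trial contrast is 20 − 14.5 = 5.5 IU/L. The add-on effect would be m(A+F) − 14.5, and m(A+F) is not given. Three assumed values, for illustration only:

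| Assumption about the combination | m(A+F) | Add-on effect | Trial contrast |
|---|---|---|---|
| No better than Fenmutong alone | 14.5 | 0 | 5.5 |
| No better than acupuncture alone | 20 | 5.5 | 5.5 |
| Fully additive, with no change in FSH if untreated | 20 + 14.5 = 34.5 | 20 | 5.5 |

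An identical trial result fits an add-on effect of 0, 5.5 or 20 IU/L. The additive case also needs the change in FSH without treatment, and the trial has no untreated POI arm.

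**Step 4. Check what the sample size targets.** The formula in section 6.4 divides by (μT − μC − △)². With △ = 3 the quantity is 20 − 14.5 − 3 = 2.5 IU/L, so 5.5 is the assumed mean difference and 2.5 is what remains after the margin. The article prints no standard deviation, so the total of 108 can be neither reproduced nor refuted. Solving the formula backwards with 1:1 allocation, one-sided α of 0.05 and 90% power:

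- SD = √[n × 2.5² / (2 × (1.645 + 1.282)²)].
- n = 43 evaluable per group (43 / 0.8 = 53.75, rounded up to 54) gives an SD of about 3.96.
- n = 45 (45 × 1.2 = 54) gives an SD of about 4.05.

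These SDs are implied, not stated. Whichever variant was used, the two means entered are those of acupuncture and of the control group. No add-on effect is assumed anywhere in the calculation.

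**Step 5. Look for a shared background.** The only element common to both arms is the healthy-lifestyle information given at consent (section 4.5). It is not presented as a treatment that acupuncture supplements. The words exclusively and solely in the arm definitions leave no room for an unstated common therapy.

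**The case against.** The strongest reply is that this is loose terminology and the trial itself is sound. The arms are unambiguous and stated three times, including in the abstract close to the adjunctive wording, so a careful reader can see what is compared. Section 3 presents acupuncture as a complementary and alternative option for women dissatisfied with hormone replacement or Fenmutong, which is the logic of substitution. Other passages speak simply of the efficacy of acupuncture. Adjunctive may have been meant as a synonym for complementary, and the phrase about additional benefits names no background treatment. The article also never says that acupuncture will be recommended on top of Fenmutong.

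Much of this is fair. The comparison of the two single treatments is legitimate, and the likeliest explanation is an ill-chosen word. How the results will be reported is not known. The exclusion of interfering drugs in section 4.4 also does not by itself prove that no background therapy is allowed; the point rests on the arm definitions. But the reply does not make the word true of these arms. It sits in the principal objective and in the definition of what the primary outcome measures, and those statements govern what the trial may claim. The limitations in section 7 acknowledge the lack of a sham arm but do not mention that add-on use is untested.

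Nor is this a matter for a fuller protocol or an analysis plan to settle. Two explicit statements in the article conflict, and an analysis plan cannot create a contrast that the arms lack.

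**Conclusion.** The concern holds. The objective and the arms contradict each other, and the effect named in the objective cannot be estimated from this design: 0 of 108 women contribute to it. The estimable effect is acupuncture alone minus Fenmutong alone, planned at 5.5 IU/L before the margin of 3. This should be corrected before results are reported, because it determines what a positive or a negative primary result can be said to mean. The conclusion assumes only that the arms are delivered as sections 4.1, 4.5 and 4.7 describe. It does not depend on the unstated standard deviation, nor on the illustrative values for combined treatment.

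**What to change.** Reconcile the objective with the arms. Section 8 (Trial status) gives a start date of March 2023, and the arms are stated consistently, so the proportionate change is to the objective:

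- In the abstract (Background and Discussion), section 3 and sections 5.1 and 5.2, replace the references to adjunctive use and additional benefits with: acupuncture alone compared with Fenmutong alone.
- Add one sentence saying that the trial does not assess acupuncture combined with Fenmutong or any other treatment, and that no conclusion on add-on use will be drawn.
- Add the same point to the limitations in section 7.

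If the full protocol does provide a common background treatment, the arm descriptions in the article are what must be corrected, and the sample size assumptions would need to be stated for that comparison.

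On the arms as written, the cost is wording only: no change to treatments, allocation, sample size, visits or tests. The price is a narrower claim.

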### Secondary outcomes

5.2

The principal outcome measure in this study revolves around the alteration observed in FSH levels. This metric serves as a pivotal gauge to evaluate the effectiveness of acupuncture treatment when employed as an adjunctive therapy for POI. The data collection process is bifurcated into two distinct time points: the baseline assessment conducted prior to the study's initiation and a subsequent assessment following the culmination of three menstrual cycles of acupuncture treatments. This meticulous approach aims to provide comprehensive insights into the impact of acupuncture on FSH levels over the specified duration, thereby contributing to the overall assessment of its therapeutic efficacy for POI. In conjunction with the primary focus on FSH levels, this study encompasses an exploration of secondary outcomes to foster a holistic comprehension of acupuncture's impact on POI. Secondary outcome measures encompass biometric features, hormone biomarkers, Self-Rating Anxiety Scale, Self-Rating Depression Scale, and transcriptome analysis. The data acquisition for these secondary outcomes is structured around two pivotal time points: the baseline assessment before study commencement and the post-intervention assessment after the conclusion of acupuncture sessions.

Comparative analysis of these datasets enables researchers to discern alterations in various parameters resultant from acupuncture treatment. Specifically, to scrutinize the distinct genes associated with individual variations in acupuncture's therapeutic effects, gene abundance profiling will be conducted within the study group and juxtaposed with the control group. Transcriptome analysis, performed on peripheral blood samples from 5 participants in each group exhibiting a ≥30 % reduction or <30 % reduction in serum FSH levels post-intervention, aims to unravel the molecular intricacies underlying acupuncture's differential efficacy. An additional 10 subjects, meeting the study criteria, will be enlisted for the healthy control group. The ensuing data analysis will be executed utilizing SPSS 25.0 for comprehensive evaluation.

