**Fig. 1 fig1:**
[figure not shown]
Study flow chart. Note: transcriptome analysis included 10 patients in the POI group and 10 patients in the Fenmutong group, with 5 patients with serum FSH levels ≥30 % and 5 patients with serum FSH levels <30 % in both groups.10 healthy women were selected as the control group.

**Table 1 tbl1:** Overview of study visits.

Itern	Screening visit	Baseline visit	Treatment visit		End of treatment visit
			POI group	Control group	
Sign consent	×				
History	×				×
Biometric features	×	×			×
Transvaginal ultrasound	×	×	×	×	×
Routine test	×				×
hormone biomarkers		×			×
transcriptome analysis		×			×
Questionnaires		×			×
Acupuncture treatment			×		
Adverse events			×		

Note: Participants from the POI group will be selected for transcriptome analysis and will only be assessed at the initial screening visit. History, biometric features, routine test results, and transcriptome analysis will be assessed. Biometric features include body mass index (BMI); transvaginal ultrasound includes endometrial thickness, ovarian volume, antral follicle count, and size of ovarian cysts or developing follicles; Routine tests include blood routine examination, liver function, kidney function, routine stool, and urine tests; Hormone biomarkers include luteinizing hormone (FSH), follicle stimulating hormone (LH), total testosterone, progesterone, estradiol, and leptin; questionnaires include Self-Rating Anxiety Scale (SAS) and Self-Rating Depression Scale (SDS).

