### Sample size

6.4

The calculation of the sample size is derived from the formula comparing two sample rates：$$N=\frac{{\left(Z_{1-\alpha \;}+Z_{1-\beta }\right)}^{2}\left(1+\frac{1}{k}\right)\cdot \sigma^{2}}{{\left(\mu_{T\;}-\mu_{C}-△\right)}^{2}})$$

Here, N represents the required sample size for each group, Pe and *Pc* denote the maximum and minimum effective rates of each group. Based on our retrospective clinical data and previous experimental reports, acupuncture demonstrated a reduction in FSH levels by 20 IU/L, while assuming that the control group reduced FSH levels by 14.5 IU/L. For the study, which is divided into two groups with parameters $\mu_{T\;}$ = 20, $\mu_{C}$ = 14.5, △=3, a test level α = 0.05 and a test efficiency 1-β = 0.9 were considered.

In light of an anticipated 20 % dropout rate, a total of 108 patients will be recruited, ensuring no less than 54 participants in each group. Given the absence of a standardized sample size calculation for transcriptome analysis, the approach aligns with prevalent studies on POI. From the pool of 108 participants, 10 patients in each group (comprising 5 with a decrease of ≥30 % in serum FSH levels after intervention, 5 with a decrease of <30 % in serum FSH levels after intervention, and 10 normal female volunteers in the healthy control group) will be selected for transcriptome analysis.

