### Allocation and blinding

6.5

Participant allocation to either the study or control group will follow a meticulous 1:1 ratio, determined by adherence to predetermined inclusion and exclusion criteria. A prospective cohort study protocol has been devised for individuals diagnosed with POI, stratified by the extent of FSH decline. The exposure factor under investigation is acupuncture treatment, with categorization based on FSH decline exceeding 30 % or less than 30 %, comprising 5 cases each.

In this openly conducted clinical trial, recognition is accorded to the inherent awareness of both patients and involved acupuncturists regarding treatment assignments due to the study's nature. However, to counterbalance potential biases and uphold the scientific rigor of the investigation, specific measures will be instituted to ensure the maintenance of blinding for other pivotal personnel involved in the study.

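### The planned 5+5 responder comparison cannot separate acupuncture-specific genes from genes linked to FSH fall under either treatment, because no stated analysis tests whether the responder contrast differs between arms

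*Protocol article*

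**What the plan says.** Sections 4.1, 5.2 and 6.4 and the note to Fig. 1 define the transcriptome subset by the observed percentage change in FSH. Section 5.2 takes "5 participants in each group exhibiting a ≥30 % reduction or <30 % reduction in serum FSH levels post-intervention", and the Fig. 1 note confirms that the split is applied to both arms: "5 patients with serum FSH levels ≥30 % and 5 patients with serum FSH levels <30 % in both groups". Ten healthy women are added. FSH is measured once at baseline and once after treatment (5.1, 6.6), so each label rests on two values.

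For the comparison, 5.2 says that "gene abundance profiling will be conducted within the study group and juxtaposed with the control group". Section 6.2 names DESeq2 for differential expression, then two-group tests, Pearson correlation and ROC curves, at two-tailed P < 0.05. Neither section states a comparison of the responder contrast between arms.

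The result is nevertheless attributed to acupuncture. Section 5.2 says the analysis "aims to unravel the molecular intricacies underlying acupuncture's differential efficacy", and the abstract says: "The study endeavors to discern specific genes linked to individualized responses to acupuncture". Section 6.5 names acupuncture as the exposure and describes a cohort "stratified by the extent of FSH decline".

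**The concern.** A before-after change in one woman mixes whatever the treatment did with whatever else moved her FSH. Genes that differ between women with larger and smaller falls are associated with FSH fall. Whether that association belongs to acupuncture is a different question, and it can be addressed only by contrasting the arms.

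The Fenmutong arm supplies the samples for that contrast, since it is split by the same rule. The article does not say how they bear on the claim. If two within-arm gene lists are laid next to each other, a gene that reaches significance in one and misses it in the other looks specific to the first, even when the underlying association is identical. With 5 against 5 this happens often.

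At stake is the trial's mechanistic aim. Genes that mark FSH fall in general could be published as genes that determine response to acupuncture, and later used to select patients for it.

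**Working it through.** The plan gives no figure to reproduce here. Section 6.4 says there is no standard sample-size calculation for the transcriptome part and follows common practice, so no error rate or power is stated for the 5+5 rule.

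**Inputs from the article.** Four cells (arm by response) of 5 women each (5.2, Fig. 1 note, 6.4); two-tailed P < 0.05 (6.2).

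**Assumptions.** Gene abundance on a suitable scale is normal with SD 1 in every cell. The gene is shifted by δ in women with a fall of at least 30 %, equally in both arms, so it is not specific to acupuncture. δ = 1, 1.5 or 2. The tests are t-tests without multiplicity adjustment, used as a simple stand-in for DESeq2.

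**1. Within-acupuncture contrast, 5 v 5.** SE = √(1/5 + 1/5) = 0.632, df = 8, critical value 2.306. The non-centrality δ/0.632 is 1.58, 2.37 and 3.16. The probability of flagging the gene is p = 0.286, 0.549 and 0.791.

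**2. Two lists side by side.** The arms are independent, so the chance of significance in acupuncture and not in Fenmutong is p(1 − p):
- δ = 1: 0.286 × 0.714 = 0.204
- δ = 1.5: 0.549 × 0.451 = 0.248
- δ = 2: 0.791 × 0.209 = 0.165 (0.166 before rounding)

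**3. Arm-by-response interaction.** The estimate is the acupuncture responder difference minus the Fenmutong responder difference. Its expectation is δ − δ = 0 and its SE is √(4/5) = 0.894 (df = 16), so the gene is flagged at the nominal 5 %.

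A simulation with 100,000 runs agrees: 0.287, 0.551 and 0.791 for step 1; 0.206, 0.247 and 0.167 for step 2; 0.050 to 0.051 for step 3.

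**4. What the interaction costs.** Its SE is 0.894/0.632 = 1.41 times that of the within-arm contrast. For a gene shifted in the acupuncture arm only:

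| Shift (SD) | Power, unadjusted P < 0.05 | Power, per-gene P < 0.0001 (illustrative) |
|---|---|---|
| 1 | 18 % | 0.1 % |
| 1.5 | 35 % | 0.5 % |
| 2 | 56 % | 2 % |
| 2.5 | 75 % | 4 % |
| 3 | 88 % | 10 % |

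**The case against.** The strongest reply is that the control samples exist. The same split is made in Fenmutong, and placing the arms together does not exclude a formal interaction. The model formula for a small secondary analysis is commonly left to an analysis plan that is not shown, and the Discussion already concedes the small transcriptome sample and the absence of a sham arm. The article also never says that a gene will be called acupuncture-specific from one arm alone, or from significance in one arm and not the other; those are readings put to the test above. Much of this stands, and it keeps the point at the level of a secondary, exploratory outcome. It does not remove it, because the article states both a comparison and an attribution, and the comparison as described cannot carry the attribution.

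It is also fair that the interaction is measured against an active hormone regimen. A gene that modifies response to acupuncture and to Fenmutong alike would not be picked up, so the interaction supports only a claim relative to Fenmutong.

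Three stronger readings are tempting, and the document does not support them.

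- A reader might infer that random FSH variation would fill the responder group even if acupuncture did nothing. That depends on a within-woman coefficient of variation (CV) the article does not give. With log-normal values and no treatment effect, the chance of at least 5 such women among 43 to 54 is about 0 at a CV of 10 %, 4 % to 10 % at 15 %, 44 % to 65 % at 20 % and over 99 % at 40 %. The assumption decides the answer.
- A reader might go on to say that the mechanistic conclusion would be reached whether or not acupuncture works. That does not follow. Labels filled by chance do not create gene findings: a gene unrelated to the fluctuation is flagged only at the nominal rate.
- Section 6.4, "assuming that the control group reduced FSH levels by 14.5 IU/L", might be read as showing that FSH falls spontaneously. It is the fall assumed under an active estradiol and dydrogesterone regimen (4.7), and says nothing about untreated women.

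**Conclusion.** The point holds as a mismatch between the stated comparison and the stated claim. Response is one before-after FSH change, the arms are only set side by side, and no stated analysis asks whether the responder-gene association differs between them. For a gene equally linked to FSH fall in both arms, the acupuncture contrast alone flags it 29 % to 79 % of the time for shifts of 1 to 2 SD, and the side-by-side reading makes it look specific to acupuncture about 17 % to 25 % of the time. The interaction does so 5 % of the time.

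The sizes rest on assumed shifts, equal variances, 5 per cell and unadjusted t-tests. The logical gap does not depend on them. It should be corrected before analysis, since the gene analysis is the trial's stated route to explaining individual response.

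**What to change.** In 5.2 and 6.2:

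1. Report the responder contrast within each arm as genes associated with FSH fall, with no attribution to acupuncture.
2. Base any claim of acupuncture-specific genes, worded as relative to Fenmutong, on the arm-by-response term in DESeq2 (arm + response + arm:response) with multiplicity-adjusted P values.
3. Name the sample time point, or add time and subject terms if both samples are used. Table 1 marks transcriptome analysis at baseline and at end of treatment, while its note restricts the assessment to screening, so these need to be reconciled.
4. Call the result exploratory and state the power.

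No further women need be sequenced: the 20 women with POI are already planned. The cost is in what can be claimed. With 5 per cell, interaction power at a 2 SD shift is 56 % unadjusted and about 2 % at an illustrative per-gene threshold of 0.0001, so few or no genes may qualify as acupuncture-specific. That is a reason to narrow the claim, since the within-arm contrast does not answer the question.
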